### Cognitive intervention group

The group receiving the SCRA cognitive intervention will be randomly selected from the entire pool of participants, without regard to whether there was a decline in cognitive functions after surgery. SCRA intervention will be conducted at home 3–5 times a week for 30 minutes. The cognitive intervention method consists of two simple tasks: 1) solving simple arithmetic, and 2) reading aloud in Japanese. Various materials will be prepared from [name] published book series “Training the Brain: The Adult’s Arithmetic Drills” 「脳を鍛える大人の計算ドリル」and “Training the Brain: The Adult’s Verbal Reading Drills” 「脳を鍛える大人の音読ドリル」. These training materials have previously been shown to be effective [35, 45]. The difficulty of arithmetic materials used will range from solving single-digit addition to double-digit division. Materials for reading Japanese aloud consist of 1–2 page stories and essays. Example training worksheets are shown in Fig. 3. The training materials will be given to the participant during their scheduled hospital visits (at discharge, 2 weeks postsurgery, 1 month post-surgery, and 2 months postsurgery). The percentage of correct answers and the time it takes to complete each task will be recorded.

**Fig. 3 Fig3:**
[figure not shown]
Sample Simple Calculation and Reading Aloud (SCRA) cognitive intervention worksheets that will be given to the participants randomly assigned to the experimental group. Reading aloud (*right*) and simple arithmetic (*left*)

Additionally, during the scheduled hospital visits, we will also ask about daily habits. Knowledge of the individual differences in emotional state is important because it could possibly affect the study results.

This cognitive intervention will continue for 12 weeks. Participants will be given all the tests mentioned above (MMSE-J, FAB, CBB, and health questionnaires) one final time at the end of the 12 weeks.

### Waitlisted control group

The waitlisted control group will also be randomly selected from the pool of participants after surgery. During the duration of the study, the waitlisted control group will continue life as usual and will not receive SCRA cognitive intervention. After completing the study, they will be given the opportunity to experience the cognitive intervention. No placebo will be used for this group. Results from previous intervention studies [32, 64] report that a placebo group is unnecessary for this type of study because no differences were observed in cognitive function improvement between the placebo group and the control groups. These participants will also travel to the hospital to meet with their doctors. As with the experimental group, during these visits, control group participants will also be queried about their daily habits. Twelve weeks after surgery the control group will be administered the final round of tests (MMSE-J, FAB, CBB, and health questionnaires).

### Outcomes

The outcome measures for all participants are the test scores from the MMSE-J, FAB, computerized tests, and health questionnaires. Additionally, the type of general anesthetic administered, the amount of anesthetic administered, the anesthesia duration, the surgery duration, age, and sex will be recorded.

### Sample size

This is a pilot study. Because a similar study has not been conducted, calculation of a sample size is not possible. However, we will aim to include 50 participants.

### Data management

Personal information and data for all experiments are handled by the personal information manager director of Tohoku University. Access to information requires a key that is securely kept and has limited access. These internal checks and balances ensure the security of all data and personal information. After the end of the experimental period, the data will be consolidated, and any information linking data back to the participant will be discarded to ensure that the data is truly anonymous. Data destruction will not be conducted.

### Statistical analysis

This study is designed to 1) determine whether there is a decline in cognition after lung surgery in elderly patients and 2) evaluate the beneficial effect of SCRA cognitive intervention in this patient population. The analysis will be based on the intention-to-treat principle.

For comparison of cognitive function before and after surgery, a Wilcoxon Signed-Rank test will be used to compare all participants in both groups. This will determine whether cognitive functions declined postsurgery. Participants will have been randomly placed into a group receiving SCRA intervention, or a waitlisted control group. To evaluate the effects of the cognitive intervention, we will calculate the change in score (post-training score minus pre-training score) for each measure and conduct a between-group variance ANCOVA test. The change in scores is the dependent variable, while the treatment group (cognitive intervention group, waitlisted control group) is the independent variable. Pretraining scores in the dependent variable, sex, and age categories are the covariates to exclude the possibility that any pre-existing difference of measure between groups will affect the result of each measure and to adjust for background characteristics. This is a pilot study that will likely be conducted with a small number of participants, and the effects are unlikely to be significant.

The level of significance is set at *p* < 0.05. However, since this study includes six different cognitive tests (MMSE-J, FAB, and four computerized tests), we will use Benjamini and Hochverg’s false discovery rate (FDR) correction methods to adjust the *p* values [65]. As a result, the statistical threshold of the behavioral data was set at *p* < 0.05, FDR-corrected. Moreover, we will report eta squared (h2) as an index of the effect size. This index is the standardized difference in the change score between the intervention groups (cognitive intervention group, waitlisted control group). In actuality, h2 ≥ 0.01 is regarded as a small effect, h2 ≥ .006 as a medium effect, and h2 ≥ 0.14 as a large effect [66]. The level of significance is set at *p* < 0.05. Missing data are imputed using the multiple imputation method, as implemented in the Statistical Package for the Social Sciences (SPSS). SPSS uses a fully conditional specification, or chained equations, imputation algorithm. Essentially, incomplete variables are individually imputed and uses the filled-in variable as a predictor in all subsequent steps. Linear regression is used for continuous variables, and logistic regression is used for categorical variables [67]. All randomized participants are included in the analyses in line with their allocation, irrespective of how many sessions they complete (intention-to-treat principle). All statistical analysis will be conducted using SPSS software (Statistical Package for Social Science).

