### Determining postsurgical cognitive function

First, the Mini-Mental State Examination-Japanese (MMSE-J) will be administered to the participant after receiving consent. The MMSE-J is a 30-point questionnaire used extensively in both clinical and research settings to measure cognitive impairment [52]. To assess dementia, clinicians will consider a person’s MMSE-J score along with their history, a physical health exam, symptoms, and results from other tests. A higher MMSE-J score indicates better cognitive performance. The MMSE is the most common mental status test used to determine POCD [53, 54]. For test-retest intervals of 2 months or less, the MMSE has been shown to have good test-retest reliability [53, 55, 56].

Following the MMSE-J, the participant will be given the Frontal Assessment Battery (FAB). The FAB is an 18-point questionnaire that is commonly performed at bedside or in a clinical setting to help measure cognitive impairment in executive functions [47–49]. Again, higher scores indicate better performance. The Japanese translation of the FAB has previously been shown to be comparable to the original English versions and has a good test-retest reliability at 3 weeks [48, 49]. Both the MMSE and FAB are commonly administered in studies determining cognitive decline [57–59].

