After the FAB, the participant will be given a laptop running the Cogstate software to measure the speed of processing, visual attention, and visual learning and memory via Cogstate’s “Brief Battery” (https://cogstate.com/). This computerized battery has been shown to effectively determine cognitive decline [25, 60]. Previous studies on the test-retest reliability of the CBB have indicated that there are no retest-related increases in scores after 1 month. However, the retest scores have been shown to increase at 1 week or less [60–62]. Additionally, the Japanese version of the CBB has previously been shown to yield reliable results for Japanese subjects [63]. This computerized test will be administered via a laptop. Trained project investigators will give detailed instructions and will be nearby to provide reassurance to the elderly participants and to help with any confusion regarding computer use. In order to measure these indicators, the software will run four tasks in sequence, which lasts approximately 15 min in total. First, the software will run a detection task to measure the speed of processing. The participant will be asked to hit the “Yes” button when the trump card turns face up. The unit of measurement will be Log10 milliseconds of the reaction times for correct responses. Incidentally, a lower score indicates better performance. The next task will be an identification task to measure visual attention. The participant will be asked to press “Yes” if the card is red and “No” if the card is black. Again, the unit of measurement is Log10 milliseconds of the reaction times for correct responses. The third task is a one-card memory task in which the participant is asked to press “Yes” if they have already been shown the card. The accuracy of performance will be measured with the arcsine transformation of the square root of correct responses. Therefore, a higher score indicates better performance. The final task is a working memory task called “One Back,” in which the participant is asked to press “Yes” if the card is the same as the previous card, and “No” if it is different. The accuracy of performance is measured using the arcsine transformation of the square root of the proportion of correct answers. Again, a higher score reflects better performance.

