These tests will be administered and scored by trained project investigators, and they will be administered to the participant three times: 1) prior to surgery as a baseline, 2) after the surgery to determine a decline in cognition (about 1 week after surgery), and 3) 12 weeks after surgery to determine the effects of SCRA. The type of general anesthesia administered, the amount of anesthesia administered, the anesthesia duration, the surgery duration, age, and sex will be noted. Additionally, several health questionnaires will be administered to determine emotional and mental wellbeing.

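### The one-week Cogstate comparison in Aim 1 mixes surgical change with retest gain, so it cannot by itself determine whether function declined

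*Protocol article*

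**What the plan says.** Under Statistical analysis, the first of two aims is to "determine whether there is a decline in cognition after lung surgery in elderly patients". For this, "a Wilcoxon Signed-Rank test will be used to compare all participants in both groups", before against after surgery. The conclusion attached to the test carries no qualification: "This will determine whether cognitive functions declined postsurgery".

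The section Determining postsurgical cognitive function fixes the timing. The first test is before surgery. The second is "after the surgery to determine a decline in cognition (about 1 week after surgery").

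The same section describes retest behaviour on the Cogstate battery. It states that "there are no retest-related increases in scores after 1 month", and continues: "However, the retest scores have been shown to increase at 1 week or less".

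On the size of the battery, Statistical analysis says "this study includes six different cognitive tests (MMSE-J, FAB, and four computerized tests"), so four of the six are Cogstate tasks. For the MMSE, the article reports reliability only: "For test-retest intervals of 2 months or less, the MMSE has been shown to have good test-retest reliability". For the FAB it reports good reliability at 3 weeks.

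The Purpose section makes clear that Aim 1 concerns only people who have surgery. The article describes no non-surgical reference group, no practice-corrected change score and no practice run. The limitations in the Discussion do not mention retest effects.

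**The concern.** A within-person comparison over time in a single group attributes the whole difference to what happened in between. That is safe only if nothing else shifts the score over the same interval. Here the article itself names something that does, at about the interval it has chosen.

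For the Cogstate tasks the tested quantity is surgical change plus retest change. If retest change is a gain in performance, a real decline is understated, may look like no change, and could even appear as improvement after surgery. This is a bias, so a larger sample would not remove it. The trial is meant as groundwork for later studies, and an understated decline would be carried into their planning.

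**Working it through.** The article gives no sample size or power calculation for Aim 1, so there is no figure to reproduce. The point rests on setting its statements side by side; the arithmetic below is illustrative.

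**Interval.**

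- Retest scores rise: 1 week or less.
- No retest-related rise: after 1 month.
- Interval used in Aim 1: about 1 week after surgery, plus the days from baseline to surgery, which are not stated. Baseline follows consent, and patients are told of the study on admission before surgery (Recruitment of participants), so nothing suggests an interval near 1 month.
- Between 1 week and 1 month the article is silent.

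**What the test estimates.** Write D for true surgical decline and G for retest gain, both in SD of the paired difference. The expected observed decline is D − G. With everyone operated on, the one-week data contain nothing that separates D from G.

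**Direction.** One Card Memory and One Back are scored so that higher is better; a rise in score is a gain in performance. Detection and Identification are log10 reaction times, where lower is better. The natural reading of a retest increase is better performance on all four. Read literally, an increase on the two reaction-time tasks would mimic decline. Either way the one-week difference is not surgical change alone.

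**Illustration.** Inputs: n = 50 pairs (Sample size); two-sided 0.05 (the level is stated, the sidedness is assumed); normal paired differences, D and G (all assumed). The signed-rank test was simulated 20,000 times per row. As a check, the probability of detecting decline is approximately Φ((D − G)·√(50·3/π) − z), where √(50·3/π) = 6.910 and z = 1.960.

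| D | G | Net | Simulated | Approximation at 0.05 |
|---|---|---|---|---|
| 0.4 | 0 | 0.4 | 77% | Φ(2.764 − 1.960) = 79% |
| 0.4 | 0.1 | 0.3 | 54% | Φ(2.073 − 1.960) = 55% |
| 0.4 | 0.2 | 0.2 | 27% | Φ(1.382 − 1.960) = 28% |
| 0.4 | 0.3 | 0.1 | 10% | Φ(0.691 − 1.960) = 10% |
| 0.4 | 0.4 | 0 | 2.5% | Φ(0 − 1.960) = 2.5% |

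If G exceeds D by 0.1 SD, about 10% of simulated trials show a significant improvement. With D = 0.5, detection falls from 93% (G = 0) to 53% (G = 0.2) and 2.4% (G = 0.5).

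**Effect of the FDR correction.** The plan corrects over six cognitive tests. At the strictest Benjamini-Hochberg step, 0.05/6 = 0.0083 and z = 2.638. For D = 0.4 the approximation gives Φ(2.764 − 2.638) = 55% with no gain, Φ(2.073 − 2.638) = 29% with G = 0.1 and Φ(1.382 − 2.638) = 10% with G = 0.2. If the correction covers Aim 1, detection for one task lies between these values and those at 0.05, depending on the other tests.

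**The case against.** The strongest reply has several parts.

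- **The interval is not exactly the one cited.** This stands. The retest comes about 1 week plus some preoperative days after baseline, and the article documents a rise only at 1 week or less. Carry-over just beyond a week is plausible but not documented.
- **It is a pilot whose effects are expected not to be significant.** The article does say this, but it concerns precision. A small sample does not excuse a bias, and the stated conclusion is not softened for Cogstate.
- **The article never says that a non-significant result will be reported as no decline.** This is correct as to the wording. But it says the test determines whether function declined, and that leaves a null result open to exactly that reading.
- **The size of the gain is unknown.** This stands. Masking is possible, not shown.

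A reader might go further and infer that all of Aim 1 is biased towards no decline. The documents do not support this: for MMSE-J and FAB they report good reliability, which neither shows nor excludes a gain. Nor do they support a claim that the trial loses a particular amount of power, since D, G and the distribution are all assumed. It would also be wrong to carry the concern over to Aim 2, where both arms follow the same test schedule and a shared retest gain largely cancels.

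**Conclusion.** The point holds for the four Cogstate tasks. The article describes a retest effect, tests at close to the interval where that effect occurs, and then interprets the uncorrected one-group difference as deciding whether function declined. That unqualified conclusion is not justified.

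That decline is understated rests on reading a retest increase as better performance. That real decline may be missed rests also on the gain being appreciable relative to the decline, and the article gives no figure for either. In the illustration, a gain of half the assumed decline cuts detection from 77% to 27% before FDR correction. Confidence is high in the inconsistency and low in the size of the bias.

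The plan should be changed, because the correction costs little and affects what one of two stated aims may report.

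**What to change.** 1. In Statistical analysis, replace the unqualified conclusion for Aim 1. Suggested wording: For the Cogstate tasks, the change from before surgery to about 1 week after surgery is surgical change net of any retest gain and is likely to understate decline; a non-significant or improved result will not be reported as absence of decline.
2. Add to the limitations that Cogstate retest gain at short intervals cannot be separated from the surgical effect in this design.
3. As a supplementary analysis only, report the change from before surgery to 12 weeks in the waitlisted arm. State that it covers about 25 patients, addresses change at about 3 months instead of 1 week, and is a third administration following a test at about 1 week. The article's statement about intervals beyond 1 month does not settle whether a gain from that closer retest persists. Nor would a null result at 12 weeks rule out decline at 1 week, since the Background says most patients recover within 6 months.

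An added practice run at baseline is not recommended. Recruitment began in January 2016, so it would give patients different baselines. It would also lengthen a session already expected to take 1 hour, and nothing in the article shows that one run removes the gain.

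The cost is a less definite Aim 1 conclusion and one extra analysis of data already being collected. No visit or test changes.

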### Randomization and blinding

Participants will be randomly placed into one of two groups: 1) the group undergoing SCRA cognitive intervention and 2) the no-SCRA waitlisted control group. Random assignment using an online computer program (http://www.graphpad.com/quickcalcs/index.cfm) will take place after informed consent and baseline testing. Participants are stratified by gender and randomized to SCRA or waitlisted control groups. In order to obtain a similar size for both groups, blocked randomization (block size 4) is applied with an allocation ratio of 1:1. Since the participants of the study are patients undergoing cognitive intervention or are being waitlisted, designing a blinded study is difficult. As a result, the trial design is open-label.

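### The treatment-effect ANCOVA leaves out the pre-operative score of the same test, already collected, which would probably but not certainly improve precision with 50 patients

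*Protocol article*

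**What the plan says.** The section Determining postsurgical cognitive function schedules the same tests on three occasions: "1) prior to surgery as a baseline, 2) after the surgery to determine a decline in cognition (about 1 week after surgery"), and 12 weeks after surgery.

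The Statistical analysis section has two parts. For decline after surgery, "a Wilcoxon Signed-Rank test will be used to compare all participants in both groups". For the effect of training, "we will calculate the change in score (post-training score minus pre-training score) for each measure", with treatment group as the independent variable. The adjustment is then listed: "Pretraining scores in the dependent variable, sex, and age categories are the covariates". The pre-operative score is not on that list.

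The pre-training score is given no date. The section Cognitive intervention group has training materials first handed out at discharge, so the test about 1 week after surgery is the natural reading.

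On size, the Sample size section says "However, we will aim to include 50 participants". Under Randomization and blinding, "blocked randomization (block size 4) is applied with an allocation ratio of 1:1", which gives 25 per arm.

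**The concern.** The covariate list is stated in the article, so this is a choice already made and not a detail left to a later plan. Its declared purpose is to keep pre-existing group differences in each measure from affecting the result. A chance difference in pre-operative score is one of these and stays unadjusted. Two patients with the same 1-week score but different pre-operative scores have fallen by different amounts.

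The 1-week score may also be an imperfect marker of usual ability. It falls in the window that the Background section calls acute decline, and the article reports that Cogstate scores rise on retest at 1 week or less. If some of its variation is transient, the pre-operative score holds further information on the 12-week score.

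At stake is precision. The article calls the number of participants severely limited and does not expect significant effects. Information already in the database is the cheapest way to narrow the interval.

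**Working it through.** The article states no power, standard deviation, effect size or correlation, so it has no figure to reproduce. The question is how the variance of the treatment estimate changes when the pre-operative score is added.

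**Inputs from the article.** n = 50, 1:1. Covariates now: pre-training score, sex, age, so q = 3 (age counted as one term). With the pre-operative score, q = 4. Error degrees of freedom go from 50 − 5 = 45 to 50 − 6 = 44.

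**Assumed inputs.** Correlations between the pre-operative (1), 1-week (2) and 12-week (3) scores, varied below. Sex and age are taken as unrelated to the scores. Allocation is taken not to affect the 1-week score.

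**Step 1: outcome.** With the pre-training score as a covariate, analysing change or the final score gives the same treatment estimate, so it is enough to work with the residual variance of the 12-week score.

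**Step 2: residual variance** (as a share of the 12-week variance).
- 1-week score alone: 1 − r23².
- Both earlier scores: 1 − (r13² + r23² − 2·r13·r23·r12)/(1 − r12²).

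**Step 3: cost of one more covariate.** Each variance is inflated by 1 + q/(n − q − 3):
- q = 3: 1 + 3/44 = 1.068
- q = 4: 1 + 4/43 = 1.093
- ratio: 1.093/1.068 = 1.023

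**Step 4: example.** All correlations 0.7. One score: 1 − 0.49 = 0.510. Both: 1 − (0.49 + 0.49 − 2 × 0.343)/0.51 = 0.424. Raw ratio 0.830; net 0.830 × 1.023 = 0.850. Equivalent patients: 50/0.850 = 58.8.

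| Assumed r12/r13/r23 | One score | Both | Raw ratio | Net ratio | Like having |
|---|---|---|---|---|---|
| 0.3/0.3/0.3 | 0.910 | 0.862 | 0.947 | 0.969 | 51.6 |
| 0.5/0.5/0.5 | 0.750 | 0.667 | 0.889 | 0.910 | 55.0 |
| 0.6/0.6/0.6 | 0.640 | 0.550 | 0.859 | 0.879 | 56.9 |
| 0.7/0.7/0.7 | 0.510 | 0.424 | 0.830 | 0.850 | 58.8 |
| 0.8/0.8/0.8 | 0.360 | 0.289 | 0.802 | 0.821 | 60.9 |
| Noisy 1-week: 0.6/0.7/0.6 | 0.640 | 0.459 | 0.718 | 0.734 | 68.1 |
| Noisy 1-week: 0.5/0.7/0.5 | 0.750 | 0.480 | 0.640 | 0.655 | 76.3 |
| Noisy 1-week: 0.7/0.8/0.7 | 0.510 | 0.322 | 0.631 | 0.645 | 77.5 |
| Decaying: 0.7/0.6/0.7 | 0.510 | 0.486 | 0.953 | 0.976 | 51.2 |
| AR(1): 0.7/0.49/0.7 | 0.510 | 0.510 | 1.000 | 1.023 | 48.9 |

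**Step 5: break-even.** The net ratio is 1 when the squared partial correlation of the pre-operative with the 12-week score, given the 1-week score, equals 1 − 1/1.023 ≈ 0.023. That is a partial correlation of about 0.15.

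**Step 6: simulation.** The change-score ANCOVA was simulated with 50 patients, an assumed effect of 0.5 SD of the 12-week score, two-sided 0.05 without multiplicity correction, and 8,000 runs per scenario.
- Equal 0.7: variance ratio 0.85, power 64% to 71%.
- Noisy 0.5/0.7/0.5: variance ratio 0.65, power 49% to 67%.
- AR(1) 0.7: variance ratio 1.03, power 65% to 64%.

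The mean estimate was 0.50 in every scenario, with or without the extra covariate.

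**The case against.** The strongest reply is that nothing here is wrong. ANCOVA on change with the score taken just before training, plus sex and age, is a standard model, and that score is the natural baseline for a training effect. This stands: the point is a missed improvement in a pilot, not an error.

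A reader might go further and infer that the model mistakes natural recovery for a training effect. The article does not support that. Under randomisation, a chance imbalance in an unadjusted covariate is part of the sampling error that the standard error already reflects, and the simulated estimates were unbiased.

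A reader might also take it that patients are back at their usual level by the last test, so that the pre-operative score must be the better predictor. The Background section does not say so. It says that most patients with postoperative decline recover over 6 months, and it describes an intermediate form detectable in the 3 months after surgery, about when the 12-week test falls.

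Nor does the model adjust for the 1-week score alone: sex and age are in it. If these explain part of stable ability, the gain from the pre-operative score is smaller than the table shows. That also stands.

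Finally, allocation "will take place after informed consent and baseline testing", and the schedule places a test "prior to surgery as a baseline". From this one might conclude that the 1-week score follows open-label allocation and is unsafe to adjust for. But the Fig. 2 caption and the section Waitlisted control group place the random split after surgery, so the conclusion is not established. The inconsistency is a separate matter. Here it shows only that the pre-operative score is the one score certain to precede allocation.

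**Conclusion.** The point holds as a likely but uncertain gain in precision. The article collects the pre-operative score of every test and leaves it out of the treatment-effect model.

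In the scenarios examined, the effect on variance runs from a loss of about 2% to a reduction of about 35%. Equal correlations of 0.5 to 0.8 give a reduction of 9 to 18%, like having 55 to 61 patients in place of 50. The larger gains need a 1-week score that is noisier than the other two. There is little or no gain if correlations fall off with time.

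All of this rests on correlations that the article does not give, on 50 analysed patients, and on sex and age adding nothing. That the score is omitted is certain, subject to reading the pre-training score as the 1-week test. The size of the gain is not certain. The change is worth making because the possible loss is small and most of the scenarios favour it.

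**What to change.** In the Statistical analysis section:
- identify the pre-training score as the test given about 1 week after surgery;
- add the pre-operative score of the same test as a second prespecified continuous covariate, beside the pre-training score, sex and age, in the ANCOVA for each of the six cognitive tests;
- name the pre-operative score in the imputation model so that it matches the analysis model. The present text does not exclude this, so it is a matter of consistency.

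The change should be fixed before 12-week results are looked at by group, since adding the covariate later would look data-driven.

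The cost is one error degree of freedom per model (45 to 44) and at worst about 2% in variance. No new data, visits or tests are needed.

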## Background

Memory loss and lack of concentration are symptoms that often occur in patients who have undergone surgery. These symptoms are part of a condition called postoperative cognitive decline (POCD), which is not an official diagnosis. Changes in cognitive abilities have been reported in elderly patients since the 1950s, and anesthesia has often been thought to be a potential culprit [1]. In 1955, Bedford [1] published a retrospective review of 1193 elderly patients who had surgery under general anesthesia over a 5-year period. He concluded that the cognitive problems were related to anesthetic agents and hypotension and that “operations on elderly people should be confined to unequivocally necessary cases.”

While most patients exhibiting POCD naturally recover from the condition in the 6 months after surgery, nearly 2 % of POCD cases last until death [1]. Thus, POCD can be divided into three categories: acute, intermediate, and long-term. Acute POCD is often used to describe cognitive decline detectable in the 1 week after surgery, intermediate POCD refers to cognitive decline detectable in the 3 months after surgery, and long-term POCD is used to describe changes lasting 1–2 years following surgery. A decline in cognition leads to difficulty in performing basic everyday activities [2–4], which results in a loss of independence [5]. POCD is also strongly associated with premature departure from the labor market [6]. Furthermore, people with POCD are at higher risk of death in the first year after surgery [7]. Consequently, maintaining or improving cognitive function in older adults is drawing increasing attention [8–23].

An international multicenter study on POCD reported memory impairments in 26 % of patients 60 years and older, with deficits reported to last for months to years [24]. Most notable instances of POCD are observed after cardiac and thoracic surgery [25]. Age is nevertheless the biggest risk factor for POCD [5, 24]. In addition, even healthy elderly adults may experience a decline in several cognitive functions, including memory [26], attention [27], executive functions [28, 29], and processing speed [30]. POCD is especially a problem because over the past 20 years, the number of older people undergoing surgical procedures has increased faster than the population is aging [25, 31].

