### Eligibility criteria

Approximately 50 volunteers will be recruited from respiratory patients undergoing lung surgery with general anesthesia lasting 2–8 hours. As previously mentioned, this is a pilot study, so 25 volunteers in each group should be enough to provide information on the changes in cognitive function. Participants must be native Japanese speakers who are 60 years and older and self-report to be right-handed. Participants should be unconcerned with their memory functions. A thoracic surgery physician from the Tohoku University Hospital will refer potential participants. Other data that will be recorded includes the type of general anesthesia, the amount of anesthesia administered, duration of anesthetic administration, duration of surgery, age, and sex. These additional data will be collected by the collaborating surgeons.

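### Read as punctuated, the aim 2 ANCOVA adjusts for age in groups rather than in years; if grouping is meant, a little precision is probably lost, and a short wording change settles it

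*Protocol article*

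**What the plan says.** The aim 2 model is in the protocol article under Statistical analysis. The outcome is the post-training minus pre-training score: "The change in scores is the dependent variable". Treatment group is the factor, and "Pretraining scores in the dependent variable, sex, and age categories are the covariates". Two purposes are given for the covariates: to adjust for background characteristics, and "to exclude the possibility that any pre-existing difference of measure between groups will affect the result of each measure".

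No band of age appears anywhere in the article. Under Outcomes, "the anesthesia duration, the surgery duration, age, and sex will be recorded". Background, Eligibility criteria and Determining postsurgical cognitive function also list it simply as age. The range is open at the top: "Participants must be native Japanese speakers who are 60 years and older". The target is 50 participants, 25 per group (Sample size; Eligibility criteria). Randomisation is stratified by gender only (Randomization and blinding).

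**The concern.** On its literal reading, the sentence chooses a coarser form of a variable that the trial already holds in finer form. Grouping a continuous covariate normally discards part of its linear relation with the outcome. Each group beyond two also uses one more degree of freedom.

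Age is not a stratification factor, so its balance between arms is left to chance and the ANCOVA is the only planned adjustment for it. With 25 per arm, the between-arm difference in mean age has a standard deviation of sqrt(2/25) = 0.28 age SDs. Grouping leaves differences within a band unadjusted. What is at stake is precision, in a trial that describes its own numbers as severely limited, and the same covariates serve all six cognitive tests.

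**Working it through.** **The plan's own figure.** There is none to reproduce. The sample size of 50 is stated without a calculation, and the article gives no SD, effect size or age-outcome correlation. The check therefore compares two versions of the model at N = 50.

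**Inputs from the article.** N = 50, 25 per arm; covariates pre-training score, sex and age; significance level 0.05 (taken as two-sided).

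**Assumptions.** R is the share of change-score variance, after pre-training score and sex, that age explains linearly; 0 to 0.30 is used. Age is normal and cut into k equal-sized bands.

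**Step 1: share of the linear age effect that k bands keep.** a(k) is the sum over bands of (1/k) x (mean standardised age in the band) squared. This gives a(2) = 2/pi = 0.637, a(3) = 0.793, a(4) = 0.861. For uniformly distributed age, a(k) = 1 - 1/k^2 = 0.750, 0.889, 0.938, so the loss is smaller.

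**Step 2: variance of the adjusted group difference**, in units of the variance before age is used, with a penalty for chance covariate imbalance.

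- Age in years (3 covariates, 45 residual df): V = (1 - R) x 47/(47 - 3)
- Age in k bands (k + 1 covariate terms, 47 - k residual df): V = (1 - a(k) x R) x 47/(46 - k)

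**Step 3: ratio of 95% CI widths**, bands over years = sqrt(V bands / V years) x t(0.975, 47 - k) / t(0.975, 45).

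Worked case, R = 0.10 and two bands: V years = 0.900 x 47/44 = 0.961; V bands = (1 - 0.0637) x 47/44 = 1.000; the df are equal, so the ratio is sqrt(1.000/0.961) = 1.020. With uniform age the same case gives sqrt(0.925/0.900) = 1.014.

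| R | 2 bands | 3 bands | 4 bands |
|---|---|---|---|
| 0 | 1.000 | 1.012 | 1.025 |
| 0.05 | 1.010 | 1.018 | 1.029 |
| 0.10 | 1.020 | 1.024 | 1.033 |
| 0.20 | 1.044 | 1.038 | 1.043 |
| 0.30 | 1.075 | 1.056 | 1.055 |

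A width ratio w corresponds to losing about 50 x (1 - 1/w^2) participants. That is about 1 at w = 1.010, 3 at w = 1.033 and 7 at w = 1.075.

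**Step 4: power**, for an assumed difference of 0.8 SD. At R = 0.05 it is 0.784 with years and 0.762-0.777 with two to four bands. At R = 0.10 it is 0.806 with years and 0.781-0.790 with bands.

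**Step 5: simulation check.** 2,500 trials per setting, ages 60-85, bands cut at 75; at 67 and 75; or at 65, 70 and 75.

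- Linear age effect, R = 0.05 to 0.20: mean width ratios 1.011-1.050, in line with the table. Bands gave the wider interval in about 64-86% of trials, not in all.
- No age effect, two bands: ratio 1.000, wider in 50% of trials.
- True step in the outcome at age 75: two bands gave 0.978 at R = 0.10 and 0.952 at R = 0.20, so bands did better. Four bands gave 1.001 and 0.974.

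**The case against.** The strongest reply is that the sentence may not describe grouping at all. It can be parsed so that 'categories' is a loose noun closing the list of covariates. The consistent use of plain age elsewhere supports that reading. This stands: a reader might infer that the sponsor has decided against age in years, but the article does not establish it. On this reading nothing is wrong with the analysis, only with its wording.

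Three further objections also stand.

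- The article says "Age is nevertheless the biggest risk factor for POCD", and a reader might infer that grouping therefore gives away a strong predictor. That statement concerns decline after surgery. Aim 2 analyses the later change, taken here as about 1 week to 12 weeks after surgery, with the pre-training score already in the model. Nothing in the article says that age predicts that change.
- The absence of cut-points is not itself a fault. A condensed article may leave them to the full protocol or the analysis plan, so the suspicion that they could be picked after seeing the data cannot rest on this text.
- Age as a single linear term has its own cost: it imposes a straight line, which bands do not.

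What the reply does not remove is the literal sentence. As punctuated it states a choice that is usually the less efficient one, gives no reason for it, and can be clarified in a few words.

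**Conclusion.** The point holds as a minor one, and conditionally. If age is grouped and acts roughly linearly on the change score, the expected cost at N = 50 is about 1-3% in CI width when age explains 5-10% of residual variance, about 4-8% at 20-30%, and 0-2.5% with no age effect. These figures rest on assumed values of R, normally distributed age and two to four equal bands. The documents supply none of these.

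A reader might go further and conclude that every between-group comparison is widened. The check does not support that: with two bands and no age effect nothing is lost on average, individual trials can go either way, and a threshold at a band edge can favour bands. Nor is there a validity problem, because a coarser covariate does not bias the randomised comparison on average.

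**What to change.** In the Statistical analysis section, replace 'age categories' with 'age in years (continuous)', so that the covariates are the pre-training score of the same test, sex, and age in years. The same edit serves both readings: it corrects the model if grouping was meant, and clears up the wording if it was not.

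The cost is a few words. No new data are needed, and a degree of freedom is saved for each band beyond two. The small downside is the linearity assumption.
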